This is a secondary analysis on pre-existing data and therefore the sample size is fixed; however using *pmpsampsize* package, a sample size of at least 494 pregnancies is estimated to be adequate to avoid overfitting [9]. Characteristics of the cohort for model development and validation will be described, including missing data. Listwise deletion will be applied for model development. A sensitivity analysis will be performed using multiple imputation.

The development of both models will follow the same analyses as both outcomes are dichotomous. Initial univariable logistic regression models will be performed on each candidate predictor to initially assess their crude association with the outcome and we will fit a multivariable model containing all predictors. Then backwards elimination will be used to successively remove the least significant predictors in the model using the Akaike’s Information Criterion and significance. A liberal *p* value of 0.10 will be applied for retention. We will also consider predictors based on clinical knowledge and previous research findings. Variance inflation factor will be performed prior to fitting the final model to identify any collinearity between the predictor variables. The final predictors will be included in a multivariable logistic regression model. The final models will be assessed for overall performance (model fit), calibration and discrimination. Clinical performance will be assessed through positive predictive value, negative predictive value, sensitivity and specificity.

Final models will be subject to internal and external validation to assess performance of the models. Internal validation using bootstrapping will enable us to examine for potential overfitting of the developed models. We will externally validate the final models in the international cohorts. The overall predictive performance, clinical performance, discrimination and calibration will be evaluated in each cohort.

The purpose of this study is to develop and validate two prediction models estimating the likelihood of: (i) having a 25% or greater decline in kidney function or initiation of renal replacement therapy, and (ii) having a delivery before 34 weeks or a SGA infant. The provision of these models will help to facilitate informed decision-making amongst women and their partners. The provision of risk information will support clinicians in providing personalised maternity counselling and care.

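### Backward elimination runs on two cut-offs that disagree, with no precedence between them, and the bootstrap is described only for the model that comes out of it

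*Protocol article*

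**What the plan says.** The statistical analysis paragraphs of the protocol article describe a full multivariable logistic model, after which "backwards elimination will be used to successively remove the least significant predictors in the model", "using the Akaike’s Information Criterion and significance". The next sentence sets a threshold: "A liberal *p* value of 0.10 will be applied for retention". A third route follows: "We will also consider predictors based on clinical knowledge and previous research findings". No sentence says which of the three decides when they disagree.

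The surviving predictors form the final model, and validation comes after that: "Final models will be subject to internal and external validation to assess performance of the models". The purpose of the bootstrap is given as "Internal validation using bootstrapping will enable us to examine for potential overfitting of the developed models". The article does not say whether elimination is repeated within each resample, or whether coefficients are adjusted afterwards. For the external cohorts, "The overall predictive performance, clinical performance, discrimination and calibration will be evaluated in each cohort".

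Table 1 lists eight candidate predictors. Five take one parameter each (age, BMI, parity, chronic hypertension, eGFR). Proteinuria has three levels, ethnicity is defined as four groups, and aetiology has eight categories.

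**The concern.** There are two linked problems.

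First, AIC and a flat p = 0.10 are different stopping rules. AIC charges each term according to its degrees of freedom; the p-value threshold does not. With a candidate list that mixes 1-df terms and a 7-df factor, the same data can yield different equations depending on which rule the analyst follows, and the clinical route adds further freedom.

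Second, elimination is itself a source of overfitting, because terms survive partly by chance. A bootstrap that takes the selected predictors as given and only refits them does not see that part. The order of the text (eliminate, fix the final model, then validate) permits exactly that procedure.

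What is at stake is the calibration of risks meant for counselling. An overfitted equation gives predictions that are too extreme: too high for women at high risk and too low for women at low risk. An internal validation that misses much of this gives no prompt to correct it.

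**Working it through.** **The plan's own figure.** The article gives 494 pregnancies as adequate to avoid overfitting. This can be neither reproduced nor refuted, because the parameter count, outcome proportion and assumed R² are not stated. For orientation, the shrinkage criterion is n = p / ((S − 1) ln(1 − R²/S)). With S = 0.9 and p = 17 it returns 494 when the Cox-Snell R² is 0.9 × (1 − exp(−17/49.4)) = 0.262. Below, 494 serves only as the stated minimum.

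**Candidate parameters (Table 1).** Age 1 + ethnicity 3 + BMI 1 + parity 1 + hypertension 1 + aetiology 7 + eGFR 1 + proteinuria 2 = 17. (Ethnicity takes 4 df if its listed labels are read as five groups, for a total of 18.)

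**The two cut-offs.** AIC drops a term when its chi-square is below 2 × df. The equivalent p-value is P(χ²_df > 2·df):

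| Term | df | AIC keeps up to p = | Flat rule keeps up to p = |
|---|---|---|---|
| Age, BMI, parity, hypertension, eGFR | 1 | 0.157 | 0.10 |
| Proteinuria | 2 | 0.135 | 0.10 |
| Ethnicity, four groups | 3 | 0.112 | 0.10 |
| Ethnicity, if five groups | 4 | 0.092 | 0.10 |
| Aetiology | 7 | 0.051 | 0.10 |

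For example, BMI at p = 0.13 has χ² = 2.29, above 2, so AIC keeps it and the p-value rule drops it. Aetiology at p = 0.07 has χ² = 13.09, below 14, so AIC drops it and the p-value rule keeps it.

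**How often the rules differ.** The simulation used the 17 parameters, assumed category frequencies and effects, independent predictors and outcome risk of 20% to 25%. Signal was set so that the true risk has a C-statistic of about 0.63, 0.70 or 0.80. There were 100 datasets per scenario (97 usable in the weakest at n = 494). The rules chose different models in 39%, 36% and 30% of datasets at n = 494, and in 34%, 27% and 25% at n = 2000. The Monte Carlo standard error is 4 to 5 points (√(0.25 × 0.75/100) = 0.043; √(0.39 × 0.61/97) = 0.050), hence roughly 20% to 45%.

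**What a final-model bootstrap misses.** In the same simulation, elimination was at p < 0.10, with 60 resamples per dataset and a test set of 20,000 as truth. Share of slope shortfall missed = 1 − (1 − reported slope)/(1 − true slope).

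| n | True C | True slope | Final model refitted | Selection repeated | Slope shortfall missed | C-statistic optimism missed |
|---|---|---|---|---|---|---|
| 494 | 0.63 | 0.674 | 0.937 | 0.659 | 81% | 66% |
| 494 | 0.70 | 0.806 | 0.896 | 0.759 | 46% | 46% |
| 494 | 0.80 | 0.849 | 0.898 | 0.840 | 32% | 37% |
| 2000 | 0.63 | 0.866 | 0.928 | 0.850 | 46% | 44% |
| 2000 | 0.70 | 0.916 | 0.941 | 0.917 | 30% | 28% |
| 2000 | 0.80 | 0.958 | 0.960 | 0.955 | 5% | 9% |

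Top row: 1 − (0.063/0.326) = 0.81. Bottom row: 1 − (0.040/0.042) = 0.05. Percentages come from unrounded output.

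Repeating selection is closer to the truth for the slope in nearly every row, though it can be somewhat pessimistic (0.759 against 0.806). With the strongest signal at n = 2000 the two bootstraps are practically the same. A further simulation at n = 494 with other assumed effects agrees in direction: true slopes 0.65 and 0.82, final-model bootstrap 0.93 and 0.89, selection repeated 0.65 and 0.80.

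**The case against.** The strongest reply is that this is a condensed article. Whether elimination is repeated in each resample, and whether coefficients are shrunk, are details that a full protocol or analysis plan may settle. A reader might infer that only the selected model will be bootstrapped and that shrinkage has been rejected. The text supports neither: it is silent on repetition, its reference to the developed models is compatible with repeating selection, and it neither plans nor excludes shrinkage. That stands, so the bootstrap part of this point is conditional.

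A reader might also take the middle simulated scenario as typical and say that about half of the overfitting is missed. The documents give no outcome risk, signal strength or actual development sample size. The 494 is a minimum, and the development source is a UK-wide linked dataset that may be much larger. Only the range can be defended.

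Nor would overfitting stay hidden. Calibration and discrimination are to be checked in every external cohort, where over-extreme predictions would tend to show. But this check comes after the equation is fixed, and differences in population and data source between the UK, Swedish and Canadian cohorts would make overfitting hard to separate from genuine differences.

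On the two rules, one could read 0.10 as the deciding level and AIC as a guide for comparing models. That reading is possible, but the sentence names both as the basis for removal. This part is not a matter of omitted detail: the article states both rules without ranking them. The bootstrap figures above apply elimination at p < 0.10 alone, so they do not measure harm from the conflict between the rules; the rate of differing models does.

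**Conclusion.** The point holds in two parts of different strength. That the article names two elimination rules which conflict for the predictors in its own Table 1, plus a clinical route with no precedence, follows from the text and from exact arithmetic. Its practical size, different models in roughly 20% to 45% of datasets, rests on assumed effects.

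That internal validation would understate overfitting is conditional on the bootstrap refitting only the selected model, which the described order allows but does not state. If so, the share missed runs from about 5% to about 81%, largest near the minimum sample size with weak signal and small with a large sample and strong signal. This is a should-fix matter: external validation gives a later check, and a larger cohort would reduce the problem.

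**What to change.** Name one elimination rule, either AIC or a stated p-value, and apply it to multi-category predictors as whole terms. List in advance any predictors forced in on clinical grounds, so that clinical judgement does not act after the data are seen. State that the whole elimination is repeated in every bootstrap sample.

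If the model is fitted by unpenalised logistic regression, multiply its coefficients by the resulting bootstrap calibration slope and re-estimate the intercept before the equation goes to the external cohorts. Do not do this on top of a penalised or already shrunken fit, which would shrink the coefficients twice. Keeping all eight predictors in a penalised model is a legitimate alternative, but it is a trade-off rather than a needed correction.

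The cost is a few sentences and a little more code. Reported internal performance will be slightly less favourable.
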